### 9.11.5 Rescue/Escape/Salvage Therapy

not applicable

## 10. ADVERSE EVENTS

### 10.1 Documenting, Recording and Reporting Adverse Events

At each contact with the subject, information regarding adverse events will be elicited by appropriate questioning and examinations and will be:

- immediately documented in the subject's medical record/source document,
- recorded on the Adverse Event Case Report Form (AE CRF) and
- reported as outlined

### 10.2 Definitions

#### 10.2.1 Adverse Event (AE)

An adverse event is any untoward or unfavorable medical occurrence in a human subject, including any abnormal sign (e.g., abnormal physical exam or laboratory finding), symptom, or disease, temporally associated with the subject's participation in the research, whether or not considered related to the research. An unexpected AE is an experience not reported in the current Investigators Brochure or elsewhere.

#### 10.2.2 Unexpected Adverse Event (UAE)

An AE is unexpected if it is not listed in the Investigator's Brochure (IB) or Package Insert (PI) (for marketed products) or is not listed at the specificity or severity that has been observed. It is the responsibility of the IND Sponsor to make this determination.

### **10.2.3 Adverse (Drug) Reaction (AR)**

An adverse reaction is an adverse event that is caused by an investigational agent (drug or biologic).

### **10.2.4 Suspected Adverse (Drug) Reaction (SAR)**

An adverse event for which there is a reasonable possibility that the investigational agent caused the adverse event. ‘Reasonable possibility’ means that there is evidence to suggest a causal relationship between the drug and the adverse event. A suspected adverse reaction implies a lesser degree of certainty about causality than adverse reaction which implies a high degree of certainty.

### **10.2.5 Unexpected Adverse (Drug) Reaction (UAR)**

An adverse reaction, the nature or severity of which is not consistent with the applicable product information (e.g., Investigator's Brochure for an unapproved investigational product or package insert/summary of product characteristics for an approved product)

### **10.2.6 Serious Adverse Event (SAE)**

A Serious Adverse Event is an AE that results in one or more of the following outcomes:

- death
- a life threatening (i.e., an immediate threat to life) event
- an inpatient hospitalization or prolongation of an existing hospitalization
- a persistent or significant incapacity or substantial disruption of the ability to conduct normal life functions
- a congenital anomaly/birth defect
- a medically important event (Medical and scientific judgment should be exercised in deciding whether expedited reporting is appropriate in other situations, such as important medical events that may not be immediately life threatening or result in death or hospitalization but they may jeopardize the subject or may require intervention to prevent one of the other outcomes listed above.)

### **10.2.7 Serious Adverse (Drug) Reaction (SAR)**

This is defined as an adverse drug reaction that is serious and at least possibly related to the IMP (see SAE criteria above).

### **10.2.8 Suspected Unexpected Serious Adverse (Drug) Reaction (SUSAR)**

A SUSAR is a Suspected Adverse Reaction that is both Serious and Unexpected. Any UAR that at any dose results in death, is life-threatening, requires inpatient hospitalization or prolongation of existing hospitalization, results in persistent or significant disability/incapacity or is a congenital anomaly/birth defect.

### **10.2.9 Unanticipated Problem (UP)**

An Unanticipated Problem is any event, incident, experience, or outcome that is:

1. unexpected in terms of nature, severity, or frequency in relation to
  - a. the research risks that are described in the IRB-approved research protocol and informed consent document; Investigator’s Brochure or other study documents; and
  - b. the characteristics of the subject population being studied; and
2. possibly, probably, or definitely related to participation in the research; and
3. places subjects or others at a greater risk of harm (including physical, psychological, economic, or social harm) than was previously known or recognized.

### 10.2.10 Unanticipated Problem that is not an Adverse Event (UPnonAE)

Unanticipated problem that is not an Adverse Event (UPnonAE): An unanticipated problem that does not fit the definition of an adverse event, but which may, in the opinion of the investigator, involve risk to the subject, affect others in the research study, or significantly impact the integrity of research data. Such events would be considered a non-serious UP. For example, we will report occurrences of breaches of confidentiality, accidental destruction of study records, or unaccounted-for study drug

## 10.3 Criteria to be evaluated by the trial clinician

If a diagnosis is clinically evident (or subsequently determined), the diagnosis rather than the individual signs and symptoms or lab abnormalities will be recorded as the AE.

All AEs occurring from the time the informed consent is signed through the 4 months follow-up will be documented, recorded, and reported. The trial clinician will evaluate all AEs with respect to **Seriousness** (criteria listed above in chapter 10.2), **Severity** (intensity or grade), and **Causality** (relationship to study agent and relationship to research) according to the following guidelines.

### 10.3.1 Assessment of Intensity

|                                                             |                                                                                                     |
|-------------------------------------------------------------|-----------------------------------------------------------------------------------------------------|
| Any adverse event has to be graded regarding its intensity: |                                                                                                     |
| MILD (Grade 1)                                              | Does not interfere with subject's usual activities or is transient, easily tolerated.               |
| MODERATE (Grade 2)                                          | Interferes to some extent with subject's usual activities (which patient is still able to perform). |
| SEVERE (Grade 3)                                            | Interferes significantly with subject's usual activities (which patient is not able to perform)     |

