### 6.2 Secondary Objectives

- to show efficacy on improvement of filarial LE
- to evaluate changes in the circumference of the affected limbs measured with tape
- to evaluate changes of skin thickness of the affected limbs measured by ultrasound
- to evaluate changes in the circumference of the affected limbs measured with an infrared scanner (LymphaTech®)
- to evaluate changes in the volume of the affected limbs measured with an infrared scanner (LymphaTech®)
- to evaluate changes of the frequency of acute attacks of adenolymphangioadenitis (ADLA)
- to evaluate changes in hygiene
- to evaluate changes in the quality of life (QoL)
- to measure biomarkers (angiogenic, lymphangiogenic, pro-fibrotic or pro-inflammatory such as VEGF, CECAM-a, MMPS) in blood and/or urine that are responsible for the progression of LE
- to measure T cell activation and differentiation marker in blood such as HLADR, Ki67 and CD38 (activation), PD-1, CTLA-4, Eomes (exhaustion), CD45RA, CD27, CCR7 (differentiation) on CD4 and CD8 T cells
- to assess the tolerability and safety of doxycycline 200mg/d for 6 weeks
- to assess the tolerability and safety of doxycycline 100mg/d for 6 weeks (group A only)

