### 7.7.3 Assessment of safety

Adverse events (AE) will be assessed and described in the scope of the daily observed treatment (DOT). This involves a) occurrence of AE, b) intensity of AE (Grade 0 (none), Grade 1 (mild), grade 2 (moderate) grade 3 (severe), c) SAE, d) relation to treatment (definite, probable, possible, remote, not related), e) outcome of AE (restored, improved, unchanged, deteriorated, death, unknown, overcome with sequelae, f) intervention.

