#### **8.2.1.1 Hematology and biochemistry**

At baseline venipuncture will be performed for assessing the full bloodcell count, transaminases, creatinine and bilirubin. Transaminases will also be checked before treatment no. 22 and on the last day of treatment (after treatment no. 42).

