## **10.4 Adverse Event Recording**

Any AE relevant for the evaluation and analysis of the clinical trial has to be documented in the source data and in the CRF on the respective Adverse Event Report Form.

Documentation and evaluation of each AE occurring between:

- Visit 3 (first day of treatment) and
- Visit 5 (4 months follow-up)

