#### **13.2.2 Termination by the investigator**

The investigator may withdraw a patient for any of the following reasons:

- An individual subject's decision.
- Any clinical AE, laboratory abnormality or other medical condition or situation such that continued participation in the study would not be in the best interest of the subject. Subjects will be followed for the duration of the study for indicated safety assessments.
- Non-compliance with study procedures to the extent that it is potentially harmful to the subject or to the integrity of the study data.
- A change in the subject's baseline condition after enrollment so that the subject no longer meets the inclusion/exclusion criteria.

In any circumstance, every effort should be made to document the participants' outcome. Therefore all participants, even if the participant was withdrawn from the trial treatment, will be encouraged to come for the follow-up visits.

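### A recorded, symptom-free liver-enzyme rise is graded mild whatever its size, because the intensity scale measures only interference with activities and has no liver row (minor)

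*Protocol*

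**What the plan says.** **What counts as an adverse event.** Section 10.2.1 defines it as any untoward medical occurrence, "including any abnormal sign (e.g., abnormal physical exam or laboratory finding").

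**What gets recorded.** Under 10.3, where a diagnosis is evident or is later established, "the diagnosis rather than the individual signs and symptoms or lab abnormalities will be recorded as the AE". Otherwise the laboratory abnormality itself is the event. Section 10.3 also requires severity to be evaluated for all adverse events.

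**How it is graded.** Section 10.3.1: "Any adverse event has to be graded regarding its intensity". Grade 1 means no effect on usual activities, or a transient and easily tolerated event. Grade 2 needs some interference, and Grade 3 needs inability to carry out those activities. Section 10.3.2 adds event-specific scales for doxycycline. Fever is graded there by measured temperature; AST, ALT and γ-GT do not appear.

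**When liver enzymes are measured.** Section 8.2.1.1: "Transaminases will also be checked before treatment no. 22 and on the last day of treatment (after treatment no. 42"). The schedule in section 3 names AST, ALT and γ-GT at both draws. Section 10.4 sets the recording window ("Documentation and evaluation of each AE occurring between") as Visit 3 to Visit 5, which covers both.

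**What the grade is for.** Section 7.7.3 lists as a component of the safety assessment: "b) intensity of AE (Grade 0 (none), Grade 1 (mild), grade 2 (moderate) grade 3 (severe"). Section 6.2 makes tolerability of each dose an objective, for the lower dose: "to assess the tolerability and safety of doxycycline 100mg/d for 6 weeks (group A only").

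**The concern.** AST, ALT and γ-GT are the only blood safety tests that the protocol repeats during treatment. Section 9.5.1 lists raised AST, and also acute hepatocellular injury and hepatotoxicity. A raised enzyme is often found only because blood was drawn, so a scale built on daily activities has nothing to measure.

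What is at stake is the intensity column of the safety data. The trial compares 200 mg/d and 100 mg/d, and section 4 gives fewer expected adverse events as one reason for studying the lower dose. If the doses differed in the size of silent enzyme rises, the recorded grades would not show it.

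**Working it through.** No sample size, power or error rate enters this point, so the check is a reading of the rules in order.

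1. **Is a raised enzyme an adverse event?** Yes, under 10.2.1. Section 10.4 limits CRF documentation to events relevant to the evaluation and analysis, so not every value just above ULN need be entered. What follows applies to those that are.
2. **Does a diagnosis replace it?** Only if one is evident or later established (10.3). A diagnosis with no row of its own in 10.3.2 would still be graded by activities, though it would be visible as a hepatic event.
3. **Which scale applies?** The 12 rows of 10.3.2 are stomach pain, loss of appetite, nausea, vomiting, diarrhea, bloody diarrhea, headache, urticaria, rashes, phototoxicity, fever and anaphylactic reactions. None fits, so 10.3.1 applies.
4. **Is there another laboratory scale in the protocol?** No. The limits of 2 × ULN in 7.8.3 are exclusion criteria at entry. They are not grades.
5. **What grade results?** The sizes below are illustrative and do not come from the protocol. Each is a symptom-free rise in one enzyme that was normal before treatment.

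| Value | Grade under 10.3.1 | Grade under the proposed row |
|---|---|---|
| 1.5 × ULN | 1 | 1 |
| 3 × ULN | 1 | 2 or 3, depending on the cut-off |
| 10 × ULN | 1 | 2 or 3, depending on the cut-off |
| 20 × ULN | 1 | 2 or 3, depending on the cut-off |

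The present grade does not change with the value. A result above the protocol's own entry limit is graded the same as one just above normal.

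6. **Can the number of affected records be estimated?** No.
   - Planned draws are 420 participants × 2 = 840 before drop-out. That counts blood samples, not misgraded events.
   - The only rate given is raised AST at 2% (9.5.1), of unstated size. On DOX 200 (120 + 30 = 150 participants) this is 150 × 0.02 = 3.0; on DOX 100 it is 120 × 0.02 = 2.4. Any of these rises at or below 2 × ULN would be Grade 1 or lower under the proposed row as well.
   - The number of records whose grade would change is therefore unknown and could be zero.

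**The case against.** The strongest reply is that nothing protecting the participant runs through this grade.

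- **Withdrawal.** Section 13.2.2 lets the investigator withdraw a participant for a laboratory abnormality, or for a change in condition "so that the subject no longer meets the inclusion/exclusion criteria"; those criteria include the 2 × ULN limits.
- **Seriousness.** A large rise can be reported as a medically important serious event (10.2.6).
- **Halting.** Under 13.3 either the site investigators or the DSMC can halt for any safety issue, with no grade required.
- **Values.** The enzyme results stay on the CRF (14.1), and the SAP, which is not shown, may tabulate them by arm and by multiple of ULN.
- **Analysis.** Section 11.7.4 plans frequencies and confidence intervals for adverse events and names no test by grade.

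All of this stands, and it limits the harm. It does not correct the grade. The clinician assigns that under the protocol when the event is recorded, and adverse-event listings prepared for the DSMC under 10.5 would carry it. Procedures in the SOP manual or the DSMC charter cannot be seen from this document.

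A reader might go further and infer that the DSMC halting criterion in 13.3 is disabled for liver toxicity, or that silent liver injury would go unnoticed. The protocol does not support either. A Grade 1 event does fail the grade 3 requirement, but that criterion also requires the event to be unexpected. Liver effects are already listed in 9.5.1, so they may fail on that ground whatever the grade. Section 10.2.2 leaves room for an event more severe than listed to count as unexpected, so this is not certain. The general safety ground for halting is open in either case.

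**Conclusion.** The point holds in a limited form. A symptom-free AST, ALT or γ-GT rise that is recorded as an adverse event, with no diagnosis replacing it, meets the Grade 1 wording whatever its size. For these tests the intensity data required by 7.7.3 cannot separate small from large silent rises in any arm.

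This rests on two readings: that 10.3.1 applies to laboratory findings, since it covers every adverse event without exception, and that no laboratory scale outside this document overrides it.

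Severity is minor. The loss is confined to the recorded grade; efficacy analyses and dosing rules do not use it. A reader might take the 840 planned draws, or the 3.0 and 2.4 expected AST rises, as the size of the problem. They are not, because neither says how many rises are large, silent and recorded.

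**What to change.** Add a liver-enzyme row to 10.3.2. Grade AST, ALT and γ-GT separately, each against its own last value before treatment day 1, and record the highest of the three resulting grades:

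- **Grade 0:** at or below ULN, or not above that enzyme's own reference value.
- **Grade 1:** above ULN and above its reference value, up to 2 × ULN.
- **Grade 2:** above 2 × ULN, up to the Grade 3 cut-off.
- **Grade 3:** above a numeric multiple of ULN that the sponsor and the DSMC write into the row before first treatment. The protocol gives no figure for this, so none is proposed here.

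State in 10.3.1 that this row replaces the usual-activities wording for these values. No change to 13.3 is needed.

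Separate grading matters. Suppose γ-GT is 1.9 × ULN at entry, which 7.8.3 permits, and stays there, while ALT rises from 0.5 to 1.5 × ULN. Grading only the highest value would look at γ-GT, find no rise and give Grade 0. Graded separately, γ-GT is Grade 0 and ALT is Grade 1, so Grade 1 is recorded. Because entry is barred above 2 × ULN, a value graded 2 or more is always a rise from that participant's reference.

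**Cost.** A protocol amendment submitted to the review boards and the national authority (16.4), and possibly a revision of the approved CRF. Some laboratory events will carry a higher grade than now. No extra samples or visits are needed.

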### 10.3.2 Assessment of Adverse Event Intensity for Doxycycline

| Adverse Event    | Grade | Intensity                                                                                                                   |
|------------------|-------|-----------------------------------------------------------------------------------------------------------------------------|
| Stomach Pain     | 0     | Absent                                                                                                                      |
|                  | 1     | Pain is easily tolerated (able to eat)                                                                                      |
|                  | 2     | Pain interferes with daily activities (unable to eat)                                                                       |
|                  | 3     | Pain that prevents daily activities (combined with vomiting and/or diarrhoea)                                               |
| Loss of appetite | 0     | Absent                                                                                                                      |
|                  | 1     | Accompanied with nausea                                                                                                     |
|                  | 2     | Accompanied with nausea and vomiting or diarrhoea                                                                           |
|                  | 3     | Accompanied with nausea and loss of weight                                                                                  |
| Nausea           | 0     | None                                                                                                                        |
|                  | 1     | Nausea that is easily tolerated (able to eat)                                                                               |
|                  | 2     | Nausea that interferes with daily activity (unable to eat)                                                                  |
|                  | 3     | Nausea that prevents daily activity (combined with vomiting and/or diarrhoea)                                               |
| Vomiting         | 0     | None                                                                                                                        |
|                  | 1     | Vomiting that is easily tolerated (able to eat)                                                                             |
|                  | 2     | Vomiting that interferes with daily activity (unable to eat)                                                                |
|                  | 3     | Vomiting that prevents daily activity (combined with nausea and/or diarrhoea)                                               |
| Diarrhea         | 0     | None                                                                                                                        |
|                  | 1     | Diarrhoea that is easily tolerated (up to 3 times per day)                                                                  |
|                  | 2     | Diarrhoea that interferes with daily activity (more than 3 times per day combined with nausea and/or vomiting and weakness) |

|                        |   |                                                                                               |
|------------------------|---|-----------------------------------------------------------------------------------------------|
|                        | 3 | Diarrhoea that prevents daily activity (combined with nausea, vomiting and/or acholic faeces) |
| Bloody diarrhea        | 0 | None                                                                                          |
|                        | 1 | Fresh or clotted in absence of haemorrhoids                                                   |
|                        | 2 | Fresh or clotted blood combined with abdominal pain                                           |
|                        | 3 | Fresh and clotted blood combined with abdominal pain and fever                                |
| Headache               | 0 | None                                                                                          |
|                        | 1 | Headache that is easily tolerated                                                             |
|                        | 2 | Headache that interferes with daily activity                                                  |
|                        | 3 | Headache that prevents daily activity                                                         |
| Urticaria              | 0 | None                                                                                          |
|                        | 1 | Requiring no medication                                                                       |
|                        | 2 | Requiring oral and/or topical medication (including steroid) for < 24h                        |
|                        | 3 | Requiring oral, topical and/or medication IV medication (including steroid) for > 24h         |
| Rashes                 | 0 | Absent                                                                                        |
|                        | 1 | Localized, itching, no blisters, lasting one day                                              |
|                        | 2 | Localized itching, with blisters lasting longer than one day                                  |
|                        | 3 | Generalized combined with fever                                                               |
| Phototoxicity          | 0 | Absent                                                                                        |
|                        | 1 | Erythema in sun exposed skin                                                                  |
|                        | 2 | Erythema in sun exposed skin and rise of skin temperature                                     |
|                        | 3 | Erythema in sun exposed skin, blisters and fever                                              |
| Fever                  | 0 | ≤ 37.5°C                                                                                      |
|                        | 1 | >37.5°C-38°C                                                                                  |
|                        | 2 | >38°C-39°C                                                                                    |
|                        | 3 | >39°C                                                                                         |
| Anaphylactic reactions | 0 | None                                                                                          |
|                        | 1 | headache accompanied by rash and itching                                                      |
|                        | 2 | in addition to 1. blood pressure failure and tachycardia, oedema                              |
|                        | 3 | in addition to 2. bronchial spasms (expiratory stridor), apnoea or cardiac arrest →SAE        |

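### The anaphylaxis row in Protocol 10.3.2 puts blood pressure failure at Grade 2 and makes Grade 3 cumulative, so a severe reaction can be recorded as moderate

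*Protocol*

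**What the plan says.** Protocol 10.3.1 sets a general intensity scale: "Any adverse event has to be graded regarding its intensity". Its Grade 2 (moderate) is some interference with usual activities, "which patient is still able to perform". Its Grade 3 (severe) applies when the patient cannot perform them. Section 7.7.3 uses the same labels for the grades.

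Section 10.3.2 follows with a table for doxycycline, giving lines of its own for named events. The anaphylactic reactions row reads:

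- Grade 1: headache together with rash and itching.
- Grade 2: "in addition to 1. blood pressure failure and tachycardia, oedema".
- Grade 3: "in addition to 2. bronchial spasms (expiratory stridor), apnoea or cardiac arrest", followed by an arrow to SAE. It is the only grade in the row with that arrow.

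Section 10.3 introduces the assessments together and does not rank 10.3.1 against 10.3.2. Section 10.3.3 sends the judgement of seriousness to the SAE definition in 10.2.6, separately from the grade.

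**The concern.** Two features of the row look wrong.

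- **Threshold.** Circulatory failure in an anaphylactic reaction is placed at the grade that the protocol elsewhere defines as leaving the patient able to carry on as usual.
- **Cumulative wording.** Each grade requires the one below it. A reaction that is dangerous through the airway, with blood pressure preserved, does not satisfy the Grade 2 line and so does not satisfy the Grade 3 line.

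Intensity is one of the items named in the safety assessment (7.7.3), and tolerability of both doses is a secondary objective (6.2). At stake is whether the recorded intensity of a rare but important reaction can be trusted. No efficacy result is involved.

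**Working it through.** No plan figure needs reproducing, so the check is a reading of the row against the general scale.

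**Signs required by the row, read literally (10.3.2)**

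| Grade | Requirement | Number of signs |
|---|---|---|
| 1 | headache, rash, itching | 3 |
| 2 | Grade 1 plus blood pressure failure and tachycardia | 3 + 2 = 5 (6 if oedema is also required) |
| 3 | Grade 2 plus at least one of bronchospasm, apnoea, cardiac arrest | at least 5 + 1 = 6 (7 with oedema) |

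**Three presentations put through both scales**

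| Presentation | Row in 10.3.2 | 10.3.1 |
|---|---|---|
| Grade 1 signs, blood pressure failure, tachycardia, oedema | Grade 2 | Grade 3 if the patient cannot perform usual activities |
| Grade 1 signs and bronchospasm, blood pressure preserved | fails the Grade 2 line, therefore fails Grade 3; only Grade 1 is met | Grade 3 if the patient cannot perform usual activities |
| Apnoea without the Grade 1 and Grade 2 signs | no line is met | Grade 3 if the patient cannot perform usual activities |

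The first presentation shows the threshold problem and the other two show the cumulative problem. In each, the entry under 10.3.1 depends on a clinical inference that the protocol does not state: that such a patient cannot carry on usual activities.

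**Where the grade could have consequences**

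- *SAE status.* Section 10.2.6 covers events that are life-threatening, lead to hospital admission or are medically important, whatever the grade. The 48-hour reporting in 10.6.1 has no grade condition. A Grade 2 reaction of this kind can still be an SAE, although the arrow stands only at Grade 3.
- *Safety analysis.* Section 11.7.4 is descriptive: counts, percentages and 95% confidence intervals. The number of adverse events is the same under either grade; only the split by intensity moves.
- *Halting.* The site rule in 13.3 rests on unexpected, related SAEs and does not use the grade. The DSMC rule does use grade 3 or above, but it needs at least two similar events that are also unexpected and at least possibly related. Anaphylaxis is listed among the known reactions in 9.5.1. A narrow route stays open because 10.2.2 also treats an event as unexpected when it is not listed at the severity observed.

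**The case against.** The strongest reply is that the row does harm only if 10.3.2 governs. If the general scale prevails, a patient incapacitated by circulatory failure is Grade 3 under 10.3.1 whatever the row says. This stands. A reader might infer that the row misgrades whichever section prevails, and the protocol does not support that. The point depends on the ordinary reading that a specific table overrides a general scale for the events it lists.

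The same clinical inference noted above can be challenged, since blood pressure failure is not defined in the protocol. It is an ordinary inference, but it remains one. The cumulative wording of Grade 3 needs no such inference.

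Three wider readings are tempting and should not be drawn:

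- *That the table ranks lesser events above anaphylaxis.* It puts "Headache that prevents daily activity" and a rash described as "Generalized combined with fever" at Grade 3. Intensity grades order severity within one kind of event, not between kinds, and the headache line agrees with 10.3.1. The comparison shows no separate error.
- *That some presentations cannot be graded.* Loss of appetite without nausea matches no line (the top one is "Accompanied with nausea and loss of weight"). Nor does a localised, non-blistering rash that goes beyond "Localized, itching, no blisters, lasting one day", or a generalised rash without fever. Section 10.3.1 requires every adverse event to be graded and covers all three. It is likewise available for bronchospasm with preserved blood pressure, so that reaction need not go ungraded.
- *That the lack of a precedence rule is an error in itself.* The two scales can differ in either direction. A fever of 38.5°C in a patient unable to perform usual activities is Grade 2 by temperature and Grade 3 by function; a fever of 39.5°C in a patient still able to perform them is Grade 3 by temperature and at most Grade 2 by function. Grading fever by temperature is a legitimate objective choice, and specific over general is the natural default. The missing sentence is a detail worth adding, no more.

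**Conclusion.** The point holds for the anaphylaxis row and is minor. Blood pressure failure with tachycardia and oedema is graded moderate, which conflicts with the protocol's own meaning of moderate. The cumulative Grade 3 line, read literally, shuts out bronchospasm, apnoea or cardiac arrest when the Grade 2 signs are not all present. If 10.3.2 governs listed events, a potentially life-threatening reaction is recorded below its true intensity.

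The conclusion rests on two assumptions: that the event-specific table takes precedence, and, for the Grade 2 threshold, that blood pressure failure prevents usual activities. A reader might also infer that such reactions would escape SAE reporting or disable the halting rule. The protocol does not support the first, because seriousness is assessed independently of grade. The effect on the second is small, because the rule has further conditions. Adverse event counts, blinding and the efficacy endpoints are untouched. The protocol gives no frequency for these presentations, so the number of misgraded events cannot be estimated.

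**What to change.** Rewrite the anaphylactic reactions row so that anaphylaxis with any one of blood pressure failure, bronchospasm, apnoea or cardiac arrest is Grade 3, without requiring the lower-grade signs. Grade 2 would then cover tachycardia and oedema without any of these. Add a note to the row that seriousness is assessed under 10.2.6 whatever the grade, so that the arrow at Grade 3 is not taken as a restriction.

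As an optional clarification, add one sentence to 10.3 stating that 10.3.2 governs where one of its lines matches and 10.3.1 applies otherwise. That sentence alone would not be enough, because it would confirm the present row as the governing one.

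The cost is one table row, a short note and, if adopted, one sentence, carried into the CRF instructions. No new assessments are needed. The downside is that slightly more events will be recorded as Grade 3.
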